### Statistical analysis

#### Sample size

The sample size is pragmatic determined by the duration of the study and recruitment rate. We estimate the following sample size *n* = 100 per site (*n* = 200 total) which includes the nested cohort of *n* = 20 per site (*n* = 40 total). For the primary endpoint, this sample size would allow us to detect a minimum correlation coefficient of 0.2 with a 5% level of significance and power of 80% using a two-tailed test. Furthermore, this sample size will support the evaluation of the secondary endpoints, allowing us to account for any confounding factors (for example, post-operative length of stay may be influenced by lower discharge rates on weekends).

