**Methods/Design:**

HepaT1ca is an observational cohort study in two tertiary-referral liver surgery centres in the United Kingdom. The primary outcome is correlation between the pre-operative liver health assessment score (Hepatica score - calculated by weighting future remnant liver volume by liver inflammation and fibrosis (LIF) score) and the post-operative liver function composite integer-based risk (Hyder-Pawlik) score.

With ethical approval and fully-informed consent, individuals considering liver surgery for primary or secondary cancer will undergo clinical assessment, blood sampling, and Liver*MultiScan*™multiparametric MRI before and after surgical liver resection or TACE. In nested cohorts of individuals undergoing chemotherapy prior to surgery, or those undergoing portal vein embolization (PVE) as an adjunct to surgery, an additional testing session prior to commencement of treatment will occur. Tissue will be examined histologically and by immunohistochemistry. Pre-operative liver health assessment scores and the post-operative risk scores will be correlated to define the ability of Liver*MultiScan*™to predict the risk of post-operative morbidity and mortality. Because technology performance in this setting is unknown, a pragmatic sample size will be used. For the primary outcome, *n* = 200 for the main cohort will allow detection of a minimum correlation coefficient of 0.2 with 5% significance and power of 80%.

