#### Inclusion criteria

Male or female adult patients being considered for liver resection or TACE (for primary or secondary liver lesions).

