### Primary endpoint

*To determine ability of LiverMultiScan™ to predict risk of post-operative morbidity and mortality by measuring the correlation between the pre-operative liver health assessment score and the post-operative risk score*.

This analysis will measure the correlation between two continuous variables. The first variable will be the FLR volume weighted by the liver inflammation and fibrosis (LIF) score. This weighting will effectively decrease the FLR with increasing LIF score. The second variable will be the composite post-operative risk score as defined by Hyder and colleagues [12]. The distribution of both variables will be tested for Normality (e.g., with the Kolmogorov-Smirnov test) and the correlation calculated with the appropriate test (e.g., Pearson correlation if Normally-distributed; Spearman’s rank correlation if not, or non-linearly correlated).

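### The 80% power for r = 0.2 holds only if at least 194 of the 200 recruited yield both primary variables, which the design does not secure

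*Protocol article*

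**What the plan says.** The Sample size section describes the number as pragmatic, fixed by study duration and recruitment rate: 100 per site, 200 in total, with the 40 nested participants counted inside the 200. It then states: "For the primary endpoint, this sample size would allow us to detect a minimum correlation coefficient of 0.2 with a 5% level of significance". The power given there is 80%, two-tailed. The Abstract (Methods/Design) repeats the claim, attaching it to 200 participants: "for the main cohort will allow detection of a minimum correlation coefficient of 0.2 with 5% significance and power of 80" per cent.

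The primary analysis (Data analysis plan, Primary endpoint) correlates two variables. "The first variable will be the FLR volume weighted by the liver inflammation and fibrosis (LIF) score"; FLR is the future liver remnant. The second variable is a composite post-operative risk score. Pearson is used if the data are Normal, and Spearman if they are not or if the relation is non-linear.

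The Inclusion criteria admit "adult patients being considered for liver resection or TACE", so a completed resection is not required. The Intervention section gives main-cohort participants a second visit after either surgery or TACE, so TACE patients are in the main cohort. The first secondary endpoint names TACE as well as surgery; the primary endpoint does not name TACE. The Consent and Withdrawal sections let a participant leave at any time.

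**The concern.** A power calculation for a correlation counts participants with both variables observed. The article applies it to the number recruited, and its own text gives three reasons why the two numbers differ:

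- TACE participants have no planned remnant, so the first primary variable is not defined for them.
- Participants considered for resection may not be resected.
- Participants may withdraw.

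The Sample size section allows for none of these.

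This is the article's only power statement for the primary endpoint. If it is taken at face value, a null result would be read as coming from a study with an 80% chance of detecting r = 0.2, when the chance may have been lower.

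**Working it through.** **Inputs.** Sample size section: two-sided alpha 0.05 (z = 1.960), power 80% (z = 0.842), r = 0.2, N = 200. Primary endpoint analysis: Pearson or Spearman. The share of the 200 without both primary variables is not stated, so it is assumed over a range.

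**Reproducing the plan's figure (Pearson, Fisher z).**

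- Pairs needed: n = ((1.960 + 0.842)/atanh(0.2))² + 3, with atanh(0.2) = 0.2027. This gives 193.97, so 194.
- Power at n pairs: Φ(atanh(0.2)·√(n − 3) − 1.960). At n = 200 this is Φ(2.845 − 1.960) = 81.2%.
- Detectable r with 80% power: tanh(2.802/√(n − 3)). At n = 200 this is 0.197.

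The stated figure reproduces for 200 complete pairs. A one-sided test would need 154, so the two-tailed reading is the one that fits.

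**Margin.** 200 − 194 = 6 participants, and 6/200 = 3%.

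**Spearman, with 0.2 taken as the rank correlation.** Pairs needed depend on the variance approximation:

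- Variance 1.06/(n − 3): n = 205.4, so 206; power at 200 is 78.9%.
- Variance (1 + r²/2)/(n − 3): n = 197.8, so 198; power at 200 is 80.4%.

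Under Spearman the margin is therefore 2 participants or none, according to the approximation.

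**Effect of non-contributing participants (Pearson; loss assumed).**

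| Loss of the 200 | Complete pairs | Power for r = 0.2 | r detectable with 80% power |
|---|---|---|---|
| 0% | 200 | 81.2% | 0.1970 |
| 3% | 194 | 80.0% | 0.2000 |
| 5% | 190 | 79.2% | 0.2021 |
| 10% | 180 | 77.0% | 0.2075 |
| 20% | 160 | 71.9% | 0.2199 |
| 25% | 150 | 69.1% | 0.2270 |
| 30% | 140 | 66.0% | 0.2349 |
| 40% | 120 | 59.2% | 0.2534 |

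**The case against.** The strongest reply is that nothing has been miscalculated. The sample size is openly pragmatic, r = 0.2 describes what a feasible number could detect and did not set that number, and the study is an observational proof of concept. Losing 10% to 20% moves the detectable correlation only from about 0.20 to between 0.21 and 0.22. A fuller protocol or analysis plan may also define the analysis set. Much of this stands: the sum is right and the consequence for the detectable effect is modest. It does not rescue the sentence as written, which attaches a definite power to a recruitment count that the article's own eligibility rules make larger than the number of pairs.

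Some stronger readings are tempting but not supported:

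- *That the power is certainly not delivered.* No TACE share, non-resection rate or scan-failure rate is given. At 5% loss power is still 79.2%, and it falls below 78% only when more than 15 of the 200 (7.5%) are lost.
- *That Spearman tolerates no loss at all.* This follows from one variance approximation and not from the other.
- *That the Abstract's reference to the main cohort conflicts with the 200, leaving 160.* The nested chemotherapy and portal vein embolisation participants are also planned for surgery and can contribute pairs, so no figure changes.
- *That TACE patients cannot have a post-procedure score.* The clinical data section collects complications and liver function after TACE as well as after surgery. Whether the cited score can be computed from these cannot be judged from the article. The firm ground is the FLR volume.

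**Conclusion.** The point holds in conditional form. The 80% power for r = 0.2 is correct for 194 or more complete pairs under Pearson (about 198 to 206 under Spearman), but it is stated for 200 recruits. With TACE as one of two entry routes and resection not required for entry, keeping non-contributors to 6 or fewer looks hard, and the article neither plans nor allows for it. The mismatch between recruited and analysable participants is in the text. The size of the shortfall rests on an assumed loss of 10% to 40%, over which Pearson power runs from 77% to 59%. These figures also assume that TACE participants supply no FLR-based score and that the Fisher approximation applies.

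**What to change.** State that the primary correlation is computed in participants who undergo resection and have both scores. Then change the power sentence in the Sample size section and in the Abstract in one of two ways:

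1. Give the correlation detectable with 80% power at the number of such participants the sponsor expects. Under Pearson this is 0.2075 at 180, 0.2199 at 160, 0.2270 at 150 and 0.2534 at 120. The expected number must come from the sponsor, since the article gives no basis for choosing among these.
2. Keep r = 0.2, but say that the claim is conditional on at least 194 evaluable resections, and on up to about 206 if Spearman is used.

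Neither option needs extra enrolment. The cost is wording in two places and, under the first, a slightly less favourable stated figure.

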#### Benefit for participants

No direct benefit is expected for the participants. We envisage that the results of this study will benefit other patients being considered for liver surgery in the future, by developing new technology which improves patient safety, and society as a whole by advancing scientific knowledge of using imaging to quantify liver health. We believe that this study may lead to improvements in pre-operative planning which will prevent or ameliorate the impact of liver surgery for cancer. This will help to maximise the health, and life expectancy, of patients with liver cancers.

#### Potential risks and burdens for research participants

The participants will be subjected to peripheral venous blood sampling which may cause discomfort or pain. MRI scans are not expected to pose a risk to patients, in the absence of known contraindications. Patients will be assessed prior to the scan for any potential contraindications to the procedure such as mechanical heart valves, pacemakers, metallic prostheses and cochlear implants.

#### Dissemination

Results of the study will be presented at local, national and international medical meetings. The findings of the study will be published in peer reviewed medical/scientific journals and made open access on acceptance. If appropriate the results of the study will be disseminated by press releases by University of Edinburgh, Basingstoke and North Hampshire Hospital or Perspectum Diagnostics. Information may also be disseminated to the general public via public engagement and community outreach programmes.

## Discussion

Liver function can be regarded as the product of the total volume of hepatocytes and the health of those hepatocytes. After hepatectomy, a minimum level of liver function is necessary for survival. At present, that projected liver function is based almost entirely on the estimated FLR volume [13, 14], with most surgical teams adopting minimum thresholds for FLR of approximately 25% in normal livers, and 40% in cirrhotic livers [15]. Ideally, projected future liver function should be calculable as the product of the FLR volume and a continuous variable measure of hepatocyte function. At present, assessment of the FLR relies on computed tomography (CT) volumetric measurement combined with a crude estimate of hepatocyte function based on clinical judgment and gleaned from surrogate markers of liver function based on blood tests. Liver fat content (steatosis) can be measured on CT, or more accurately with magnetic resonance imaging (MRI) [16]. However, hepatic fibroinflammatory disease, which has been shown to correlate with overall and liver-related morbidity after resection [17], typically requires an invasive biopsy to diagnose accurately. Therefore, a preoperative non-invasive investigation that provides the estimated FLR and a validated measure of hepatocyte performance will be an important advance in the safety assessment of patients considering liver surgery.
